## Abstract

The purpose of this study is to assess the effectiveness of a theory-based self-care intervention with the application of health literacy strategies in patients with high blood pressure and limited health literacy. This is a randomized controlled trial, with measurements at baseline and 1 and 3 months follow-up. 100 patients with high blood pressure and limited health literacy will be randomly allocated to either an intervention group or a usual care control group. We will mainly establish the intervention model based on the principal health belief model components. Patients randomized to the intervention group will receive four educational sessions during four weeks. Considering the limited health literacy level of the patients of the study, health literacy strategies will be used in educational material design for enhancing the quality of the intervention. In order to cover these strategies, we will design four standard animated comics and fact sheets with illustrations and photos consistent with the health belief model constructs and educational sessions' topics. Data will be collected using some questionnaires and will be analyzed using the SPSS software. The findings of this study may assist with the development of a theoretical model for self-care intervention in patients with high blood pressure and limited health literacy.

## 1. Introduction

Hypertension is a chronic condition affecting approximately one billion individuals worldwide [1]. A 24% increase in developed and 80% in developing countries are predicted for the year 2025 and the increase is expected to be much higher than these predictions [2]. In this regard, it was reported to be 14 to 34 percent in Iran [3] and a systematically review study reported high rates of hypertension among males and females globally [4]. This chronic disease can lead to very serious consequences such as cardiovascular and kidney disease [5]. Due to the high prevalence of hypertension and its serious complications, the World Health Organization (WHO) assigned the theme of World Health Day 2013 to hypertension as a “silent killer, global public health crisis” [6].

Despite the benefits of evidence-based hypertension self-care behaviors in improving blood pressure, hypertensive patients usually have low compliance with the recommended self-care behaviors. Various studies all over the world suggest a high prevalence of uncontrolled blood pressure among people with hypertension [7, 8]. One approach that may advance blood pressure control and be practicable for the most of hypertensive patients is patient compliance with self-care behaviors [9]. The findings of a meta-analysis that examined the results of 87 studies indicated that optimal self-care in hypertensive patients could reduce systolic and diastolic blood pressure by 5 and 4.3 mmHg, respectively [10]. Self-care for people with high blood pressure includes a diet rich in fruits and vegetables, cessation of smoking, sufficient physical activity, antihypertensive medication, reduction in weight, saturated and total fat, and sodium, and moderate alcohol consumption [11]. Despite the benefits of evidence-based hypertension self-care behaviors in improving blood pressure, hypertensive patients generally do not follow medical or lifestyle recommendations and compliance with self-care behaviors in these patients is not desirable [12].

The WHO has emphasized patient education as an important strategy to improve the active participation of patients in their disease management process [13]. Self-care behaviors are influenced by demographic variables and modifiable psychological variables such as self-efficacy, perceived threats, perceived benefits and barriers [11, 14]. Although some studies have examined educational interventions in patients with high blood pressure, they often lack a theoretical framework describing how the educational emphasis on social, psychological, and cognitive variables can affect self-care behaviors in these patients.

Health Belief Model (HBM) is one of the most important theories of behavior change that have been widely considered in behavioral health sciences and successfully applied in the design of health interventions. This model has emphasized the role of moderating factors (demographic, social, and structural factors) and individual perceptions (perceived sensitivity, perceived severity, perceived benefits, perceived barriers, guidance for action, and self-efficacy) in determining the likelihood of performing a behavior [15]. According to this model, a person's decision and motivation to perform a particular behavior included items such as person's perception of being at risk (perceived susceptibility) and its seriousness (perceived severity), belief in the perceived action of usefulness to reduce the risk of disease, and understanding of the health benefits (perceived benefits) due to obstacles and moderating factors such as demographic and psychosocial variables (awareness) and people's judgments of their capabilities to execute given level of performance (self-efficacy)[16, 17]. The results of a cross-sectional study carried out in an earlier study showed that the HBM and its related structures, especially self-efficacy, perceived susceptibility, and severity of complications, are important determinants of self-care behaviors in hypertensive patients with limited health literacy [18].

Although education and especially the theory or model-based education are effective in controlling the blood pressure of patients, there is some evidence suggesting that limited health literacy of patients could act as a barrier in the result of the interventions [19]. Evidence suggests that limited health literacy patients may understand less than half of what is told to them during medical communication [20] Moreover, patients with low health literacy may be ashamed by their condition and hide their low level of literacy from healthcare providers who could possibly help [21]. In this regard, the results of a study on diabetic patients showed that despite the fact that 73% of patients with inadequate health literacy participated in diabetes education classes, 50% of them did not know the signs and symptoms of low blood sugar and 62% of them were unaware of the treatment methods for reducing blood glucose [22].

Choosing proper strategies, based on deeper understanding of needs and capabilities of patients with limited health literacy may help healthcare providers to communicate more efficiently with these patients [23]. Although low health literacy patients regularly rely on verbal instructions, they may have difficulty remembering and comprehending information [24]. Health literacy experts recommend incorporating a few effective and feasible strategies to advance communication and patients' understanding during the communication. Strategies such as plain language and using pictorial media in education will be used in this study.

Regarding high prevalence of hypertension in Iran and limited health literacy among a large population of these patients, it is indispensable to evaluate the effectiveness of an educational intervention based on influencing psychological factors using HBM applying health literacy strategies to promote self-care behaviors in patients with high blood pressure.

## 2. Material and Methods

### 2.1. Design

This randomized control trial (RCT) will be conducted with the high blood pressure patients attending to Haft-e-Tir comprehensive health services center of Bushehr, south of Iran. The trial was registered at the Iranian Registry of Clinical Trials with the IRCT code: IRCT2017011731999N1. The participants will be invited to the study to measure their health literacy level at first. Patients who have limited health literacy level according to S-TOFHLA result will be assigned to the two groups: HBM and health literacy strategies-based self-care intervention (trial) and usual care group (control).

### 2.2. Setting

All patients recruited are those diagnosed with high blood pressure who are referred to Haft-e-Tir comprehensive health services center in Bushehr city (south of Iran) between July 2017 and August 2017.

### 2.3. Patient Eligibility

The patients will be entered into the study if they are diagnosed with high blood pressure. Inclusion criteria for this study are as follows: (a) passing at least 6 months since the definitive diagnosis of the disease, (b) being able to read, write, and speak Persian, (c) being 30 years old and over, (d) having no severe complications caused by hypertension, including cardiovascular disease, kidney disease, retinal disease, and stroke, and (e) having the desire to participate in the study. Exclusion criteria for the study consist of (a) causing severe complications from hypertension, including cardiovascular disease, kidney disease, retina, and stroke during the study and (b) missing attending educational classes more than once.

### 2.4. Ethical Consideration

The study protocol will follow the principals of the “Declaration of Helsinki.” The participants will be told that they can withdraw from the study at any time and all information will be kept secret and anonymous. This study was approved by Bushehr University of Medical Sciences Ethics Committee (Number IR.BPUMS.REC.1395.128). Informed consent will be obtained from all the participants who will agree to participate in the study.

### 2.5. Sample Size

According to the study performed by Eftekhar Ardebili et al., 2014 [25], the effect size for the study has obtained based on 90% power, 5 % type one error level, and 1 unit difference between the mean score of knowledge before and, after the intervention, 40 patient per group have been estimated. Considering a dropout rate of 10% during the study, we aim to recruit 50 patients per group.

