### 2.9. Primary Outcome Measures

#### 2.9.1. Self-Care Behavior

Self-care behaviors will be determined using the 31-item hypertension self-care activity level effects (H-scale) prepared by Findlow [28]. This scale aims to help physicians for a better guidance to hypertensive patients who are looking for attaining blood pressure control [29]. The H-scale surveys the level of self-care by questioning about the number of days per week on which an individual carries out a self-care behavior. The H-scale was previously validated in Persian patients with high blood pressure [28]. The Persian version consisted of 27 items that measure the hypertension self-care activities with the following domains: medication adherence (3 items), physical activity (2 items), low-salt diet (10 items), smoking (2 items), alcohol (1 item), and weight management (9 items). The Persian version of the scale shows adequate internal consistency. Cronbach alphas were as follows: medication adherence (Cronbach's *α* = 0.91), low-salt diet (Cronbach's *α* = 0.72), physical activity (Cronbach's *α* = 0.96), smoking (Cronbach's *α*= 0.91), and weight management (Cronbach's *α* = 0.85).

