### 2.10. Secondary Outcome

#### 2.10.1. Knowledge of Hypertension

 Hypertension knowledge will be assess by using Hypertension Knowledge Level Scale (HK-LS); this 22-item scale is prepared by Erkoc et al. [30]. Hypertension Knowledge Level Scale (HK-LS) will assess respondents' knowledge in defining hypertension, lifestyle, medical treatment, drug compliance, diet, and complications of hypertension. Each item is a full sentence that is either correct or incorrect. And each item is prepared as part of a standard answer (correct, incorrect, or do not know). Motlagh et al. have validated this questionnaire in Iranian population [28]. In Persian version in the validation process, two items were excluded from the scale and the final version has 19 true/false items.

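### The 90% power in Section 2.5 is worked out for a before-after difference in knowledge, a secondary outcome, so it does not apply to the primary comparison of self-care between the arms

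*Protocol article*

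**What the plan says.** Section 2.5 is the only sample-size statement in the protocol article. It refers to an earlier study for its inputs and says that "the effect size for the study has obtained based on 90% power, 5 % type one error level". The target and the resulting number are given together: "1 unit difference between the mean score of knowledge before and, after the intervention, 40 patient per group have been estimated". It then allows for 10% dropout and sets recruitment at 50 per group, which agrees with the total of 100 in the Abstract.

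The outcome sections rank the endpoints differently. Under the primary outcome heading (Section 2.9), "Self-care behaviors will be determined using the 31-item hypertension self-care activity level effects (H-scale"). Under the secondary outcome heading (Section 2.10), "Hypertension knowledge will be assess by using Hypertension Knowledge Level Scale (HK-LS").

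The Abstract and Sections 2.1 and 2.7 describe a randomised comparison of the educational intervention with usual care. The Abstract and Section 3 give its purpose as the effectiveness of a self-care intervention. Nowhere does the article give a target difference in self-care, an H-scale SD or a power figure for self-care.

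**The concern.** A stated power belongs to one outcome and one contrast. Here the outcome is knowledge, which the article itself ranks as secondary. The contrast, as worded, is before versus after, whereas randomisation serves a comparison between arms. Nothing connects the 90% to the H-scale.

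What is at stake is how the primary result will be read. If the self-care comparison shows no significant difference, the size of effect that the trial could have detected decides whether this is evidence against the intervention or merely inconclusive. The only figure available, 90%, does not answer that. If the before-after wording is literal, the 90% does not carry over to the between-arm comparison of knowledge either.

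**Working it through.** **Inputs from Section 2.5.** Power 90%, type I error 5%, difference 1 unit on the knowledge score, 40 per group, dropout 10%, 50 recruited per group. Sidedness is not stated; two-sided is assumed. The SD is not printed, so the 40 can only be solved backwards, on each of the two possible readings.

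**1. What the 40 per group implies (t-test, two-sided 5%, 90% power).**
- *Two-sample reading.* With 40 in each arm, 90% power needs a standardised difference of 0.734. For a 1-unit difference, SD = 1 / 0.734 = 1.36.
- *Paired reading, as the sentence is worded.* With 40 pairs, 90% power needs a standardised change of 0.526. For a 1-unit change, SD of change = 1 / 0.526 = 1.90.

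The normal approximation gives nearly the same: d = (1.960 + 1.282) × √(2/40) = 0.725, so SD 1.38; or 3.242 / √40 = 0.513, so SD of change 1.95. Both readings are arithmetically possible, and the text does not settle which was used.

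**2. What follows for knowledge if the calculation was paired.** Assume an SD of change of 1.90 in both arms and a true difference between arms of 1 unit in mean change, so d = 1 / 1.90 = 0.526. Two-sample t-test power:

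| Evaluable per arm | Power |
|---|---|
| 40 | 64% |
| 45 | 69% |
| 50 | 74% |

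On the two-sample reading this loss does not arise.

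**3. How many patients the primary analysis can count on.** 50 × (1 − 0.10) = 45 per arm. (In the other direction, 40 / 0.90 = 44.4, so 45 would have been enough to recruit; the 50 is a small surplus.)

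**4. What that number delivers for self-care.** No H-scale effect or SD is given, so the result can only be put in SD units. Two-sided 5%, unadjusted t-test at one time point:

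| Evaluable per arm | 90% power for | 80% power for | Power at 0.5 SD | Power at 0.3 SD |
|---|---|---|---|---|
| 40 | 0.73 SD | 0.63 SD | 60% | 26% |
| 45 | 0.69 SD | 0.60 SD | 65% | 29% |
| 50 | 0.65 SD | 0.57 SD | 70% | 32% |

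The row for 45 is the relevant one. The effects of 0.3 and 0.5 SD are assumptions for illustration, not figures from the article.

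**5. Effect of baseline adjustment.** Adjusting for the baseline score divides the standardised difference by √(1 − ρ²), where ρ is the correlation between baseline and follow-up. The article gives no ρ. If it were 0.5, then 0.5 / 0.866 = 0.577 and power at 0.5 SD with 45 per arm rises to about 77%. If it were 0.7, then 0.5 / 0.714 = 0.700 and power is about 91%. Section 2.12 does not name such an adjustment.

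**The case against.** The strongest reply has four parts.

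- *The wording is loose, and the per-group figure points to a two-sample formula.* This is plausible and stands as far as it goes: the paired consequence must remain conditional. It does not touch the outcome mismatch, because the calculation is on knowledge under either reading.
- *A journal article condenses, and the SD may be in the cited study or the full protocol.* Accepted. The unprinted SD is not part of this point. Condensation does not explain the rest, since the basis for the sample size is stated and disagrees with the article's own ranking of outcomes. An unseen analysis plan would not change which outcome Section 2.5 used.
- *Section 2.5 says openly that it concerns knowledge and claims no power for self-care.* True, and a careful reader will notice. But it is the only power statement, and it is offered as the justification for the size of the whole trial.
- *The trial may be large enough.* It may. A reader might infer from the mismatch that the trial is underpowered for self-care, but the documents do not support this. They give neither an expected H-scale difference nor an SD. If the true difference is about 0.7 SD or more, 45 per arm gives 90% power without adjustment, and a baseline-adjusted analysis could detect less.

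**Conclusion.** The point holds in limited form. The 90% in Section 2.5 refers to a secondary outcome and, as worded, to a change over time, so it cannot be quoted for the primary comparison of self-care between intervention and usual care. That rests on the text alone and needs no assumption.

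The size of the consequence does rest on assumptions. With 45 evaluable per arm and a two-sided 5% unadjusted t-test, the trial has 90% power for 0.69 SD, 80% for 0.60 SD and 65% at 0.5 SD. The fall to about 69% for a 1-unit difference between arms in knowledge change applies only if the calculation was truly paired (SD of change about 1.90) and the SD of change is the same in both arms. No shortfall for self-care has been shown.

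This should be fixed, but it is not critical: it corrects the justification of the sample size and leaves recruitment and randomisation as they are.

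**What to change.** Keep 50 per group and rewrite Section 2.5 around the primary contrast.

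- Name the H-scale score to be compared. Section 2.9.1 lists six domains and no total score.
- Name the follow-up time of the primary comparison. Section 2.8 lists both 1 and 3 months after the intervention.
- State what the size delivers for intervention versus usual care. For example: 50 recruited per arm with 10% dropout leaves 45, and a two-sided 5% unadjusted t-test then has 90% power for 0.69 SD, 80% for 0.60 SD and 65% at 0.5 SD. Add that baseline adjustment would improve on this, if it is planned.
- Keep the knowledge calculation only as support for a secondary outcome, and say whether it is paired or between groups.

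The cost is a rewritten section and a less favourable stated power. No extra patients are needed. The choice of score and time point has to be made before the new statement can be written.

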### 2.6. Measurement and Procedure

After checking the medical records file in the Haft-e-Tir comprehensive health services center and invitation of patients who meet the inclusion criteria for the study, invited participants will undergo a screening test by Test of Functional Health Literacy in Adults (S-TOFHLA) [26] for selecting those who have limited health literacy. S-TOFHLA is a valid and widely used measure which takes 12 minutes or less to administer. The S-TOFHLA includes reading comprehension and numeracy sections and uses actual materials that patients might encounter in the healthcare setting, such as medication label instructions. The sum of the 2 sections yields the S-TOFHLA score, which ranges from 0 to 100. Scores on the S-TOFHLA are classified and interpreted as follows: inadequate health literacy (scores 0 to 53): individuals will often misread the simplest materials, including prescription bottles and appointment slips and the instructions for an upper gastrointestinal tract radiograph series; marginal health literacy (scores 54 to 66): individuals perform better on the simplest tasks but have difficulty comprehending the Medicaid rights and responsibilities passage; adequate health literacy (scores 67 to 100): individuals will successfully complete most of the tasks required to function in the healthcare setting, although many still have difficulty comprehending more difficult information (i.e., materials written above a 10th grade reading level). In this study patients with both inadequate and marginal health literacy are considered limited health literacy. The valid Persian version of the scale shows adequate internal reliability for numeracy (Cronbach' s *α* =0.69) and for reading comprehension (Cronbach' s *α* = 0.78) [27].

Participants of the study will undergo three measurements: on entry to the study (pretest) and 1 and 3 months after having gone through the intervention for following up. Selected patients will go through the pretest and a then one-month intervention, 1 and 3 months after intervention follow-up.

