### 2.7. Randomization and Blinding

From all hypertensive patients who had medical records in the Haft-e-Tir comprehensive health services center and were eligible for the study, we will select for the invitation by simple random sampling. Then we will screen them for health literacy stage. After completing the inform consent form, limited health literacy patients will randomly allocate to either the control or the intervention group. Randomization of the participants will be done using permuted block randomization. Due to the nature of this intervention, blinding of the patients to the allocation will not be completely possible.

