### 2.8. Outcome Measures

The outcome will be assessed at the baseline, one and 3-month after intervention [Figure 1]. Baseline measurement includes demographic (age, sex, marital status, education, job, income, smoking, and duration of the disease), HBM constructs questionnaire (perceived susceptibility, perceived severity, perceived barriers, perceived benefits, and self-efficacy), and self-care behaviors questionnaire.

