### 2.12. Statistical Analysis

Survey data will be coded and analyzed using the Statistical Package for the Social Sciences (SPSS) version 22. In addition to providing descriptive statistics, Chi-square test will be used to compare the distribution of qualitative demographical characteristics between the two groups before intervention. T-test will be used to compare the mean scores of knowledge and health belief model constructs (perceived sensitivity, severity perceived benefits, perceived barriers, and perceived self-efficacy) between the two groups. The Repeated Measure ANOVA analysis will be used to examine and compare changes in the mean scores of knowledge and constructs during the study period in each group and the comparison between the two groups. The post hoc analysis will perform within per groups to compare the times. The Kolmogorov–Smirnov test will be used for checking the normality distribution of the data. The P value of <0.05 will be considered statistically significant.

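### The S-TOFHLA score is known for every patient before randomisation, but the stated allocation and between-group analyses make no use of it: a low-priority loss of balance and precision, not a bias

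*Protocol article*

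**What the plan says.** Section 2.6 scores the S-TOFHLA from 0 to 100 and describes the two lower bands differently: "inadequate health literacy (scores 0 to 53): individuals will often misread the simplest materials", against "marginal health literacy (scores 54 to 66): individuals perform better on the simplest tasks". It then pools them for entry: "In this study patients with both inadequate and marginal health literacy are considered limited health literacy".

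Section 2.7 sets the order of events. Patients are invited, then "Then we will screen them for health literacy stage", then consent, then allocation. On the method it says "Randomization of the participants will be done using permuted block randomization"; no stratification factor is named.

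Section 2.8 gives the baseline variables: "Baseline measurement includes demographic (age, sex, marital status, education, job, income, smoking, and duration of the disease"), followed by the health belief model and self-care questionnaires. The S-TOFHLA score is not in the list. In section 2.12, "Chi-square test will be used to compare the distribution of qualitative demographical characteristics between the two groups before intervention". The between-group tests named there are a t-test and a repeated-measures ANOVA, with no covariate.

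Three other places bear on the point:
- The Introduction says there is some evidence that "limited health literacy of patients could act as a barrier in the result of the interventions".
- Section 2.11 hands out a written fact sheet after each session, with a readability target below grade 6.
- The Discussion expects the results to inform on the part that health literacy level plays.

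**The concern.** The variable that defines the population is collected on everyone before randomisation, and is then absent from every stated step that could use it. If patients in the two bands read differently, they may also differ in knowledge, in self-care, or in what they take from written material. With about 50 per arm, the mix of bands can differ between arms by chance. That adds noise to the between-group difference which stratification or adjustment could remove at almost no cost. The Discussion's promise on literacy level also has no stated analysis behind it.

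**Working it through.** **Inputs from the article.** 50 patients per group, 100 in total; 90% power; 5% type I error (section 2.5). Bands 0 to 53 and 54 to 66 (section 2.6).

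**Assumptions, not in the article.** Share inadequate among those enrolled: 20% to 80%. Outcome difference between bands: 0.2, 0.5 or 0.8 SD. Block size: 4 or 6. Two-sided test.

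**The plan's own figure.** The article gives no figure on literacy balance. Its sample size (40 per group before dropout) cannot be reproduced because no SD is stated; a two-sided two-sample calculation with a 1-unit difference implies an SD of about 1.38. Dropout of 10% gives 40/0.90 = 44.4, so 45; the plan recruits 50. That excess is conservative and does not affect what follows.

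**Chance imbalance.** Let K of the 100 patients be inadequate and X of these fall in one arm of 50. X is hypergeometric, and the difference in share inadequate is (2X − K)/50.

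| Share inadequate | SD of difference | P(10 points or more) | P(20 points or more) |
|---|---|---|---|
| 20% or 80% | 8.0 points | 21.1% | 2.3% |
| 30% or 70% | 9.2 points | 27.5% | 4.9% |
| 50% | 10.1 points | 31.7% | 7.1% |

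For even K the difference moves in 4-point steps, so 10 or more means 12 or more. Simulated unstratified blocks (4,000 runs per setting, K varying, 30% to 70% inadequate) gave 30% to 37% for 10 points or more and 4% to 6% for 20 points or more. With blocks stratified by band, the largest simulated difference was about 4 to 5 points and no run reached 10.

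**Effect on the estimate.** The standard error with 50 per arm is √(2/50) = 0.20 SD. If band affects the outcome equally in both arms, shift = imbalance × band difference.

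| Band difference | 10-point imbalance | 20-point imbalance |
|---|---|---|
| 0.2 SD | 0.02 SD | 0.04 SD |
| 0.5 SD | 0.05 SD | 0.10 SD |
| 0.8 SD | 0.08 SD | 0.16 SD |

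If band affects only the response to the intervention, the shift is half as large: a 20-point gap puts the intervention arm 10 points from the overall mix, so a 0.5 SD difference gives 0.10 × 0.5 = 0.05 SD.

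**Precision.** At a 50:50 mix the band explains v = 0.25 × d² of the variance: 0.01, 0.0625 and 0.16 for d = 0.2, 0.5 and 0.8. Power after adjustment is Φ[(1.960 + 1.282)/√(1 − v) − 1.960] = 90.3%, 91.7% and 94.3%. As a cross-check at d = 0.5, a typical 10-point imbalance contributes 0.10 × 0.5 = 0.05 SD, and 0.05²/0.20² = 0.0625, the same share. None of this allows for the pretest, which would already absorb part of any stable difference between bands.

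**The case against.** The strongest reply is that nothing here is an error. Much of it stands.

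- **Pooling.** A reader might infer that combining the bands is itself the fault. It is not; it defines eligibility, and the remedy leaves it unchanged.
- **Differential benefit.** A reader might infer that the protocol says literacy band alters what patients gain from education. It does not. The Introduction's statement is hedged and concerns limited literacy as a whole, and everyone enrolled has limited literacy. Section 2.6 says only that the bands read differently; a different response is an inference.
- **Score discarded.** A reader might infer this from the baseline list. That list is not exhaustive: it also leaves out hypertension knowledge, whose change over time section 2.12 analyses. A stratum or covariate could also appear in a fuller document.
- **Imbalance invisible.** Education, a partial proxy, is among the listed demographic variables covered by the baseline check. The repeated-measures ANOVA includes the pretest, so a stable level difference between bands would show there and would not by itself create a difference in change.
- **Bias.** Permuted blocks without strata leave the comparison unbiased, and the standard error already reflects chance imbalance.

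What remains is narrower. The article does not pass over these topics: it names the allocation method and the between-group tests, and none of them uses the score. A t-test at follow-up does not absorb a level difference, and the pretest does not absorb a difference in change between bands.

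**Conclusion.** The point holds as a modest, low-priority design improvement. It is not a contradiction and does not threaten the validity of the comparison. The avoidable cost is a 21% to 32% chance of a 10-point or larger imbalance in percentage inadequate, a 2% to 7% chance of 20 points or more, and about 0.3 to 4.3 points of power. At an assumed 0.5 SD band difference, even a 20-point imbalance moves the estimate by half a standard error, and a 10-point one by a quarter. All of this rests on an assumed band mix and band effect; the article gives neither, so the gain could be negligible. The reasons to act are that the score is already collected and that the Discussion's aim on literacy level needs it.

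**What to change.** 1. **Section 2.8:** list the S-TOFHLA score as a baseline variable and report it by arm.
2. **Section 2.12:** include the score as a covariate in the between-group comparison. For the t-test this means a linear model with arm and score; in the repeated-measures model the score should also be allowed to interact with time, since otherwise it absorbs only a level difference.
3. **Section 2.7, only if allocation has not begun:** generate the permuted-block lists separately for scores 0 to 53 and 54 to 66.

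The cost is one covariate (with its time interaction), two lists instead of one, and at most one incomplete block per stratum. No extra patients, visits or tests are needed. If allocation is already complete, steps 1 and 2 remain available. A covariate shows how outcomes vary with literacy level, not whether benefit does, so the Discussion's wording should stay within that.
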